## Abstract

Primary cervical dystonia (PCD), or spasmodic torticollis, is a focal dystonia characterized by involuntary and often painful muscle contractions, leading to abnormal cervical movements and postures. While botulinum toxin injections are the first-line treatment, additional therapies, such as segmental muscle vibration (SMV), remain underexplored. SMV, a non-invasive neuromodulation technique, may enhance motor cortex excitability and promote neuroplasticity, offering potential benefits in PCD management. This single-center triple-blinded randomized controlled trial evaluates SMV’s efficacy in reducing dystonic pain and improving quality of life in PCD patients undergoing standardized rehabilitation after botulinum toxin treatment. Participants with a pain level of ≥3 on the Numerical Rating Scale will be randomized into two groups. The experimental group will receive 80 Hz SMV during a 10-session rehabilitation program, while the control group will undergo sham SMV. Both groups will follow identical physiotherapy and occupational therapy protocols. The primary outcomes include changes in pain intensity and function, assessed at baseline, mid-treatment, and post-treatment using validated scales. The secondary outcomes will evaluate quality of life and patient satisfaction. This study hypothesizes that SMV will significantly reduce dystonic pain and enhance quality of life, supporting its integration into multidisciplinary rehabilitation for dystonic disorders. Trial registration number: NCT06748846.

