
Assessments will be conducted at baseline (T0), mid-treatment after 5 sessions (T1), and post-treatment at the end of the 10th session (T2). The COPM will not be repeated at T1 due to its sensitivity limitations in mid-course evaluations.

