### 2.5. Sample Size

The sample size was determined based on the primary outcome TWSTRS, referring to previous studies [25,26]. The sample size was calculated using G*Power 3.1 software, considering an effect size (d) according to Cohen’s “large” (d = 0.8), two degrees of freedom with a power (1-beta) of 80%, and alpha of 5%. Considering a drop-out rate of 20% resulted in a sample size of 14 subjects per group, for a total of 28 subjects.

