### 2.7. Statistical Methods

Descriptive statistics will summarize baseline characteristics and outcomes. Continuous variables will be presented as means ± standard deviations and categorical variables as frequencies and percentages. Inferential statistics will include paired *t*-tests or Wilcoxon signed-rank tests for within-group comparisons and independent *t*-tests or Mann–Whitney U tests for between-group comparisons. Statistical significance will be set at *p* < 0.05.

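### The named between-group tests use no baseline covariate although every scale has a T0 value; adjusting for baseline would gain from almost nothing to a substantial amount of power, depending on a correlation the protocol does not give

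*Protocol article*

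**What the plan says.** Section 2.7 names paired t-tests or "Wilcoxon signed-rank tests for within-group comparisons", and independent t-tests or "Mann–Whitney U tests for between-group comparisons", at a 0.05 significance level. It names no baseline covariate and does not say which quantity enters the between-group test.

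Section 2.4 sets the visits: "Assessments will be conducted at baseline (T0), mid-treatment after 5 sessions (T1), and post-treatment at the end of the 10th session (T2"). Only the COPM is skipped at T1. Every scale therefore has a T0 and a T2 value, and all but the COPM have a T1 value.

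The Abstract describes the outcomes as changes: "The primary outcomes include changes in pain intensity and function, assessed at baseline, mid-treatment, and post-treatment using validated scales". This leaves open that the t-test is meant for change scores.

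Section 2.5 states: "The sample size was determined based on the primary outcome TWSTRS". It uses d = 0.8, 80% power, alpha 5% and 20% drop-out, and arrives at 14 per group. It gives no SD, does not say whether d is in raw-score or change-score units, and gives no correlation between baseline and follow-up.

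**The concern.** In a trial this small, the baseline score is the cheapest available source of precision. A T2-only comparison ignores it. A change score uses it with a fixed coefficient of 1, which over-corrects when the T0–T2 correlation is modest. ANCOVA estimates the coefficient.

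Chance imbalance shows what is at stake. The between-arm difference in baseline means has SD √(2/n), in baseline SDs. This is 0.43 with 11 per group and 0.38 with 14. A gap of 0.5 SD or more, over half the effect sought, arises in about 24% and 19% of such trials. A T2-only comparison carries the correlation times that gap into its estimate, whereas ANCOVA removes it.

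A two-sample test at T2 also makes no use of the T1 score of a patient who leaves between T1 and T2, in a plan that expects 20% drop-out.

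**Working it through.** **Inputs.** From Section 2.5: d = 0.8, alpha 5%, power 80%, 14 per group, drop-out 20%. Evaluable: 14 × 0.8 = 11.2, taken as 11. Assumptions: two-sided testing, equal SDs at T0 and T2, and a T0–T2 correlation ρ, which the article does not give and which is shown over a range.

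**The plan's own figure.** An independent two-sided t-test at d = 0.8 and 80% power needs 26 per group evaluable, or 33 enrolled (26/0.8 = 32.5). One-sided it needs 21, or 27 enrolled. The stated 14 does not follow from the between-group test in Section 2.7. A total of 28 does match a 2×3 repeated-measures group-by-time interaction (f = 0.4, 2 numerator df, zero correlation): 22, then 22/0.8 = 27.5, so 28. That is not the named test either.

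**Power formulas** (noncentral t, n per group, d in T2 SDs):

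- T2-only t-test: ncp = d√(n/2), df = 2n − 2. For n = 11: 0.8 × √5.5 = 1.876, power 43%. For n = 14: 0.8 × √7 = 2.117, power 53%.
- Change-score t-test: ncp = d√(n/2) / √(2(1 − ρ)), df = 2n − 2. At ρ = 0.5 the divisor is 1, so power equals the T2-only test.
- ANCOVA: ncp = d√(n/2) / √((1 − ρ²)(1 + 1/(2n − 4))), df = 2n − 3. The last factor is the average price of chance covariate imbalance in a small sample, 1 + 1/18 = 1.056 at n = 11. Leaving it out overstates power by about 2 points. Example, n = 11, ρ = 0.5: 1.876 / √(0.75 × 1.056) = 2.109, power 52%.

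| ρ | T2-only, n = 11 | Change, n = 11 | ANCOVA, n = 11 | T2-only, n = 14 | Change, n = 14 | ANCOVA, n = 14 |
|---|---|---|---|---|---|---|
| 0 | 43% | 24% | 41% | 53% | 30% | 51% |
| 0.3 | 43% | 33% | 44% | 53% | 41% | 55% |
| 0.5 | 43% | 43% | 52% | 53% | 53% | 63% |
| 0.6 | 43% | 51% | 58% | 53% | 63% | 70% |
| 0.7 | 43% | 63% | 68% | 53% | 75% | 80% |
| 0.8 | 43% | 81% | 82% | 53% | 90% | 91% |

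Simulation agrees with the ANCOVA columns to within about a point (44–45% at ρ = 0.3, n = 11). Simulated Mann–Whitney power on T2 values is about 41% (n = 11) and 49% (n = 14).

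**Share of the shortfall from 80% that ANCOVA recovers over T2-only.** At n = 11 the shortfall is 80 − 43.1 = 36.9 points. ρ = 0.3: (44.3 − 43.1)/36.9 = 3%. ρ = 0.5: (51.7 − 43.1)/36.9 = 23%. ρ = 0.7: (68.0 − 43.1)/36.9 = 67%. At n = 14 the shares are 8%, 38% and 99%. Power of 80% needs ρ of about 0.79 with 11 per group and about 0.71 with 14.

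**If d = 0.8 is in change-score SDs.** The difference in T2 SDs is then 0.8√(2(1 − ρ)). At n = 11 the change-score test has 43% whatever ρ is. ANCOVA has 52%, 49% and 47% at ρ = 0.5, 0.6 and 0.7, a gain of about 9, 6 and 4 points that shrinks as ρ rises.

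**The case against.** The named tests are valid. They keep their type I error rate, and randomisation makes the T2 difference unbiased over repeated trials. A reader might infer from the imbalance argument that the planned estimate is biased. It is not: chance imbalance is already reflected in the standard error, and the loss is one of precision. That stands.

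A reader might also infer that the plan certainly ignores baseline. The documents do not support this either, because the Abstract's reference to changes leaves change scores possible. Under that reading baseline is used, though generally less efficiently. At ρ = 0.9 with 11 per group the two methods are level (about 98% each).

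The strongest inference would be that adjustment wins back much of the lost power for nothing. That rests on a correlation absent from the documents. At 0.3 almost nothing returns. Near zero, the lost error degree of freedom and the imbalance penalty take about 2 points.

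Finally, the article is condensed, and its list of tests is not worded as exhaustive. Missing-data handling may properly sit in an analysis plan not shown, so the T1 point is a benefit of the mixed model and not a separate fault. The choice of between-group test is stated, however, and adopting a baseline-adjusted model would replace that statement.

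**Conclusion.** The point holds as an avoidable inefficiency in a stated method. It is not an error of validity. On the T2-SD reading with 11 per group, ANCOVA adds about 1, 9 and 25 points over a T2-only t-test at correlations of 0.3, 0.5 and 0.7. Over change scores it adds about 12, 9 and 5 points. On the change-score-SD reading the gain over change scores is about 4 to 9 points for correlations of 0.5 to 0.7. These figures assume normal data, equal SDs at T0 and T2, two-sided 5% and 20% drop-out.

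Adjustment does not replace correcting the sample size. For 80% power with ANCOVA (d in T2 SDs, 20% drop-out), enrolment per group would be 30, 25, 19 and 14 at correlations of 0.3, 0.5, 0.7 and 0.8. The stated 14 suffices only at the top of that range.

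**What to change.** Replace the between-group wording in Section 2.7. Make the primary analysis a linear model of TWSTRS at T2 on arm and TWSTRS at T0, with all randomised patients in their assigned arm, reporting the adjusted difference and its 95% CI. Alternatively, use a mixed model on T1 and T2 with baseline, arm, visit and arm-by-visit, taking the T2 contrast as the result, so that patients with only T1 contribute. Use the same model for the other scales (COPM at T2 only), and keep a rank-based test as a sensitivity analysis. State in Section 2.5 the scale of d and the assumed T0–T2 correlation, and redo the sample size for this model.

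The analysis change costs wording and one error degree of freedom, with no added patients, visits or measurements. Section 4 requires renewed ethics approval for an amendment, and the change should be made before any outcome data are examined by arm. Redoing the sample size may raise enrolment, but that need exists under the current tests too.

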The afferent stimulations of SMV are thought to enhance proprioceptive feedback, normalize sensorimotor integration, and induce neuroplastic changes, potentially restoring more physiological muscle activation patterns [12]. The neurophysiological rationale for SMV is grounded in its ability to influence the gamma motor system and alter cortical excitability. Studies have demonstrated that vibration can modulate somatosensory and motor cortex activity, reduce maladaptive plasticity, and improve motor function These effects have been explored in various neurological disorders, including stroke, Parkinson’s disease, and spasticity, where SMV has shown promise in improving motor control, reducing muscle tone, and enhancing functional outcomes [13]. In the context of dystonia, the preliminary evidence suggests that SMV may address the underlying sensorimotor integration deficits by recalibrating aberrant afferent input and modulating basal ganglia and cerebellar circuits. However, the application of SMV in PCD remains largely unexplored, with only a few case studies and small-scale trials investigating its efficacy as a non-invasive and well-tolerated therapeutic option. For instance, a proof-of-concept study demonstrated that vibrotactile stimulation of the neck reduced pain in individuals with dystonia [14]. Additionally, a case study exploring neck muscle vibrotactile stimulation as a treatment for cervical dystonia reported pain relief and improvements in electrophysiological and kinematic data [15]. These studies have reported improvements in head posture, pain, and functional disability, highlighting the potential of SMV as a non-invasive and well-tolerated therapeutic option.

Building on the pathophysiological understanding of PCD and the neurophysiological mechanisms of SMV, this randomized controlled trial (RCT) hypothesizes that SMV can improve clinical outcomes in patients with PCD by normalizing sensorimotor integration and reducing maladaptive muscle activation. Specifically, the objective of this study will be to assess the efficacy of SMV in adjunction to standard care in improving PCD symptoms, compared to sham SMV plus standard care, in terms of pain, cervical dystonia severity, disease-related disability, and patients’ self-perceived performance and satisfaction in daily activities.

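### The between-arm tests in section 2.7 ignore baseline TWSTRS; ANCOVA on T0 would give more precision at almost no cost with 14 per arm

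*Protocol article*

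**What the plan says.** Section 2.7 plans paired t or Wilcoxon signed-rank tests within each group, and independent t-tests or "Mann–Whitney U tests for between-group comparisons". No covariate, ANCOVA or mixed model is named. The section does not say whether the between-arm test is applied to T2 values or to change from T0. The abstract points towards change: "The primary outcomes include changes in pain intensity and function, assessed at baseline, mid-treatment, and post-treatment using validated scales".

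Section 2.4 schedules assessments at T0, after five sessions (T1) and after the tenth session (T2). Only the COPM skips T1, so TWSTRS is available at all three visits. Section 2.5 gives TWSTRS its central role: "The sample size was determined based on the primary outcome TWSTRS". It assumes d = 0.8, and then: "Considering a drop-out rate of 20% resulted in a sample size of 14 subjects per group". The stated aim in the Introduction is a contrast between arms, with SMV "compared to sham SMV plus standard care".

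**The concern.** When the same scale is scored before and after treatment, the baseline score usually explains part of the final score. A t-test or Mann–Whitney test on T2 values makes no use of it. A t-test on change subtracts T0 with a fixed weight of 1, which adds noise unless T0 and T2 are highly correlated. ANCOVA estimates the weight from the data.

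Two things make this matter here. First, precision is scarce: 14 per arm, or about 11 after the planned drop-out. Second, chance baseline differences are common in groups this small, and section 2.6 describes simple 1:1 allocation by envelope with no stratification mentioned. Such a difference moves a T2 comparison in one direction and a change comparison in the other. As section 2.7 leaves the choice between the two open, the result could depend on which one is run.

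**Working it through.** **Inputs from the article.** d = 0.8, power 80%, alpha 5%, drop-out 20%, 14 per arm (section 2.5); 1:1 allocation (section 2.6). Completers: 14 × 0.8 = 11.2, so about 11 per arm.

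**Assumptions not in the article.** Two-sided testing; TWSTRS SD of 10 at both visits, so that d = 0.8 is 8 points; bivariate normal scores; T0–T2 correlation r = 0.3, 0.5 or 0.7.

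**The plan's own figure.** A two-sided two-sample t-test, as in section 2.7, needs 26 per arm at d = 0.8, or 26/0.8 = 32.5, so 33 after drop-out. The stated 14 is not reproduced by that test. A repeated-measures interaction F test with 2 numerator degrees of freedom, f = 0.4 and an assumed correlation of 0 gives 22 in total, and 22/0.8 = 27.5, so 28. That test is not in section 2.7. This is a separate matter; below I take 14 and 11 per arm as given.

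**Standard error of the arm difference, n per arm.**
- T2 values: SE = 10 × √(2/n). For n = 11: 10 × √(2/11) = 4.26.
- Change: SE × √(2(1 − r)). For n = 11: 5.05 / 4.26 / 3.30 at r = 0.3 / 0.5 / 0.7.
- ANCOVA, averaged over chance imbalance: SE × √((1 − r²)(1 + 1/(2n − 4))). For n = 11 the variance factor is 0.91, 0.75 or 0.51 times 19/18, giving 4.18 / 3.79 / 3.13.

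**Power for 8 points.** The T2 and change t-tests follow from the noncentral t distribution; ANCOVA and Mann–Whitney are by simulation (40,000 and 20,000 trials per cell, with the ANCOVA figures repeated at 100,000).

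| Method | 11 per arm, r = 0.3 / 0.5 / 0.7 | 14 per arm, r = 0.3 / 0.5 / 0.7 |
|---|---|---|
| t-test on T2 | 43% (any r) | 53% (any r) |
| Mann–Whitney on T2 | 40% (any r) | 51% (any r) |
| t-test on change | 33 / 43 / 63% | 41 / 53 / 75% |
| ANCOVA on T0 | 45 / 52 / 68% | 55 / 64 / 80% |

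With 11 per arm, ANCOVA gains 2 / 9 / 25 points over the T2 t-test and 12 / 9 / 5 points over the change test. For a smaller effect of 5 points the power is 20% for T2, 16 / 20 / 30% for change and 21 / 24 / 33% for ANCOVA. Under the null, the three t-type tests reject in 4.8% to 5.2% of trials.

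**Where ANCOVA stops winning.** Against T2 values it breaks even when (1 − r²)(1 + 1/(2n − 4)) = 1, that is r = √(1/(2n − 3)): 0.20 for n = 14 and 0.23 for n = 11. At r = 0 its power is 51% against 53% (n = 14) and 41% against 43% (n = 11). Against change with n = 11, the tie is at (1 + r) × 19/18 = 2, so r = 36/19 − 1 = 0.89.

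**Chance imbalance.** The SE of the T0 difference is 4.26 (n = 11) or 3.78 (n = 14), so the T0 means differ by more than 5 points in 24% or 19% of trials. An imbalance of 5 points shifts the expected T2 difference by 5r = 1.5 / 2.5 / 3.5 points, and the change difference by 5(1 − r) = 3.5 / 2.5 / 1.5 points the other way.

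**Toxin timing.** Section 2.2 allows earlier toxin up to 30 days before the study. Adding a residual effect of up to 10 points at T0, carried to T2 fully or not at all, leaves an ANCOVA gain over the T2 t-test of 1–3 / 8–11 / 21–27 points. The conclusion does not depend on toxin timing.

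**The case against.** The strongest reply is that nothing here is wrong: both planned tests are unbiased under randomisation and hold the 5% level, so this is a choice of efficiency. That is correct, and it limits the point to lost precision.

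It can also be said that a short article section stating what the analyses will include need not be exhaustive, and that covariates may be specified in a fuller document. But the article does name its between-arm methods, and both are unadjusted.

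Third, the gain rests on a correlation the article does not give, and variable response to toxin injected near T0 could lower it. This stands as a limit on the size of the gain. On the likelier reading, with change as the response, the gain is 5 to 12 points and not 25. At r = 0.3, ANCOVA with 11 per arm (45%) does not recover the 53% of a T2 test with 14. The possible loss, however, is about 2 points at worst against the T2 test, and change is more precise only above r of about 0.89.

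Finally, ANCOVA does not repair the sample size. That is also true: by the approximation d/√(1 − r²), 80% power needs about 20 completers per arm at r = 0.5 and about 14 at r = 0.7.

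**Conclusion.** The concern holds as an inexpensive improvement, not as an error of validity. For correlations of 0.3 to 0.7, ANCOVA on T0 is more precise than either test that section 2.7 allows. The direction is secure for any r between about 0.23 and 0.89 with 11 completers per arm. The size of the gain depends on r, and on whether the alternative is a test of T2 values or of change. At r = 0.5 the adjustment roughly makes up for the planned drop-out; at r = 0.3 it does not. A single prespecified ANCOVA would also remove the open choice between T2 and change, and would adjust for chance baseline imbalance.

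**What to change.** In section 2.7, state that the primary between-arm analysis of TWSTRS is an ANCOVA of the T2 score on arm with the T0 score as covariate, reported as an adjusted difference with its 95% confidence interval. If residuals are clearly non-normal, test the same adjusted effect by permutation in place of Mann–Whitney. Label the within-arm paired tests as descriptive, since they do not address the comparison with sham. The other scales in section 2.4 can be handled in the same way, each with its own T0 value. Eligibility need not change.

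The cost is one or two sentences and one degree of freedom (critical t 2.056 to 2.060 at 14 per arm), with no new data, visits or patients. Section 4 requires ethics approval for any amendment, so there is an administrative step. The statistical downside is the loss of about 2 points of power if T0 and T2 turn out to be uncorrelated.

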By addressing this objective, this RCT seeks to establish SMV as a novel therapeutic approach for PCD, potentially expanding the treatment strategy of non-invasive interventions for this challenging condition. Moreover, the findings of this study may contribute to a deeper understanding of sensorimotor integration deficits in dystonia and pave the way for further research into vibration-based therapies in movement disorders.

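### Section 2.7 uses unadjusted two-sample tests without fixing T2 value or change from T0, so 5% is not guaranteed and baseline is not used as a covariate

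*Protocol article*

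**What the plan says.** The inferential plan is in section 2.7 (Statistical Methods). Between groups it names "independent *t*-tests or Mann–Whitney U tests for between-group comparisons". Within groups it names "paired *t*-tests or Wilcoxon signed-rank tests for within-group comparisons". The threshold for all of them is "Statistical significance will be set at *p* < 0.05". Scores are summarised by group as means with standard deviations.

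Section 2.4 fixes three visits: T0, T1 after five sessions, and T2 after the tenth. A baseline score is therefore collected on every scale. The nearest the article comes to naming an analysed quantity is the Abstract: "The primary outcomes include changes in pain intensity and function". Section 2.7 does not take this up.

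Section 2.5 sizes the trial on TWSTRS, which it calls the primary outcome, with d = 0.8, alpha 5%, 80% power and 20% drop-out, giving 14 per group and 28 in total.

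**The concern.** Two things in the stated method are fixed badly.

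First, for one scale at T2, four between-group p-values fit section 2.7 equally well: t-test or Mann–Whitney, on the T2 value or on the change from T0. If the choice can be made after the data are seen, the 5% is a property of each test and not of the plan.

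Second, neither version uses the baseline well. A comparison of T2 values ignores T0. A comparison of changes subtracts T0 with a coefficient of one whatever the correlation, and at low correlation this adds noise. With 14 per arm the lost precision matters. The Introduction says that the trial "seeks to establish SMV as a novel therapeutic approach for PCD", so the comparison that carries this claim should be single and as precise as the collected data allow.

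**Working it through.** **Inputs.** From the documents: alpha 5%, d = 0.8, 14 per arm, 20% drop-out, 1:1 allocation. Completers per arm: 14 × 0.8 = 11.2, taken as 11. Assumed, because the documents give no figure: T0–T2 correlation r of 0.3, 0.5 or 0.7; normal scores; SD of 1 at both visits; two-sided tests; 0.8 read in SDs of the T2 score.

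**Step 1: the plan's own 5%.** In null simulations the single t-test, on T2 or on change, rejects in 4.8% to 5.6% of runs (4,000 per setting). The nominal level is reproduced for one fixed test.

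**Step 2: open quantity.** With equal SDs, the correlation between the T2 difference and the change difference is √((1 − r)/2). This is 0.59, 0.50 and 0.39 at r = 0.3, 0.5 and 0.7. Two independent tests would give 1 − 0.95² = 9.75%, so correlated ones should fall slightly below that. Simulation (40,000 runs per setting, t-test on either quantity) gives 8.7% to 9.5%.

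**Step 3: open test.** Taking the smaller p of t and Mann–Whitney on one quantity gives 5.4% to 6.5%, so about 1 point is added. A normality-test gate instead gives 4.9% to 5.7%. Taking any of the four analyses gives about 10–12%. Most of the inflation therefore comes from the open quantity.

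**Step 4: precision and power of the stated tests.** For a t-test on T2 values the CI half-width is t(0.975, 2n − 2) × √(2/n):
- n = 14: 2.056 × 0.378 = 0.78 SD
- n = 11: 2.086 × 0.426 = 0.89 SD

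Power for 0.8 SD from the noncentral t, with noncentrality 0.8 × √(n/2), is 53% at n = 14 and 43% at n = 11. For change scores the SD is √(2(1 − r)) = 1.18, 1.00 and 0.77, so the standardised effect is 0.8 divided by that.

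**Step 5: T0-adjusted comparison.** The half-width is approximately t(0.975, 2n − 3) × √(2(1 − r²)/n). For n = 14 and r = 0.7: 2.060 × 0.378 × √0.51 = 0.56. The simulated values below also include chance imbalance at T0.

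| n per arm | r | Power, T2 t-test | Power, change t-test | Power, ANCOVA | Half-width, T2 t-test | Half-width, ANCOVA |
|---|---|---|---|---|---|---|
| 14 | 0.3 | 53% | 41% | 55% | 0.78 | 0.75 |
| 14 | 0.5 | 53% | 53% | 64% | 0.78 | 0.68 |
| 14 | 0.7 | 53% | 75% | 80% | 0.78 | 0.56 |
| 11 | 0.3 | 43% | 33% | 45% | 0.89 | 0.86 |
| 11 | 0.5 | 43% | 43% | 52% | 0.89 | 0.78 |
| 11 | 0.7 | 43% | 64% | 68% | 0.89 | 0.65 |

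Type I error of the ANCOVA is 4.8% to 5.2% across these settings.

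**Step 6: why this settles the quantity.** With T0 as a covariate, T2 and change from T0 give the same treatment difference, standard error and p-value, because they differ only by the covariate itself. The choice between value and change no longer matters.

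**The case against.** The strongest objection is that this is a condensed article. A full protocol was approved by the ethics committee, an analysis plan may exist, and either could fix one comparison. A rule for choosing t or Mann–Whitney, confidence intervals and the label for an inconclusive result are all commonly left there. This stands, and the point does not rest on their absence. It rests on the method that section 2.7 does state, which is open between two quantities and less precise than one the same data allow.

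It can also be said that the Abstract speaks of changes. If change is taken as fixed, only the 1 point from the test choice remains. That is fair, but the Abstract mentions changes in describing outcomes over three visits, and section 2.7 names no quantity. The loss of precision remains under either reading, though at r = 0.7 the gain over a change score is smaller (75% to 80%) than the gain over T2 values.

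A reader might infer several stronger things that the documents do not support:
- That the 5% is breached. Each test holds about 5%; the inflation needs a choice made after seeing the data, which the article does not announce.
- That a non-significant result could not be interpreted. Section 2.7 promises means and SDs, from which a difference and CI can be worked out once n is known.
- That efficacy rests on the p-value alone. Section 2.7 says what inference will include and excludes nothing.
- That section 2.7 is at fault because an observed d = 0.8 gives p = 0.075 with 11 per arm. That comes from the number of completers; with 14 per arm the same d gives p = 0.044. The size of the trial is a separate matter for section 2.5.

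**Conclusion.** The point holds in a limited form. Section 2.7 does not guarantee 5% for even one scale at T2: the rate could be about 9–10% with the quantity open and about 10–12% with the test open as well. The test choice alone is minor. The firmer part is the method. Compared with a t-test on T2 values, adjusting for T0 raises power for 0.8 SD from 53% to about 55–80% with 14 per arm, and from 43% to about 45–68% with 11. It narrows the CI half-width from 0.78 to 0.56–0.75 SD, and from 0.89 to about 0.65–0.86 SD.

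These figures rest on assumed correlations of 0.3–0.7, normal scores and equal SDs at T0 and T2. At r = 0.3 the gain is small. Adjustment does not bring the trial to 80% power except near r = 0.7 with no drop-out, so it does not answer the sample-size question.

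**What to change.** In section 2.7, replace the between-group sentence for TWSTRS with one inference: the SMV minus sham mean difference at T2, adjusted for the T0 score by ANCOVA, in scale points, with its 95% CI and two-sided p-value from the same model. State that the Mann–Whitney test is a sensitivity analysis that cannot replace this result. If an analysis plan already says this, section 2.7 should agree with it.

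The cost is two or three sentences. No visit, measurement or treatment changes, since T0 is already collected. The trial gives up one residual degree of freedom (26 to 25 with 14 per arm, 20 to 19 with 11) and the freedom to switch tests after seeing the data.
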